#### **Radiological evaluations:**

Radiological evaluations will be performed by independent investigators.

Preoperative and 3 months postoperative MRI scans will be evaluated to measure the extent of decompression by calculating the change in dural sac cross-sectional area at the most stenotic level (square millimetres [16]. The association between the increase in dural sac cross-sectional area and clinical improvement (primary outcome) will be assessed. We will compare the increase in dural sac cross-sectional area in patients who achieve a minimal clinically important change of the ODI with those who do not.

## **4)STATISTICAL CONSIDERATIONS**

#### **Adherence and protocol deviations**

The trial is monitored following the Helsinki Declaration, The International Conference on Harmonisation Guideline for Good Clinical Practice (ICH GCP) [17]. An independent monitor, without influence on the scientific work, will be responsible for the monitoring. Due to the nonregulated ICH GCP guideline for this trial (not including drug intervention) the risk and safety will be safeguarded at the same level as data quality. All informed consent forms will be checked, and all registrations of serious events will be monitored. According to the monitoring plan selected variables will be checked. All hospitals will be visited regularly. Adapted versions of the 'Investigator's Site File (ISF)' and the 'Trial Master File (TMF)' will be checked for essential documents during the trial. Queries and deviations will be recorded and reported, and the coordinators at responsible hospitals have two months to send a written report with the required corrections to the monitor. All deviations from the protocol will subsequently be recorded at the 'Note to file form'. Recorded deviations will be presented in the final manuscript, tables or in Supplementary. Statistical Analysis Plan for NORDSTEN-SST, SAP Version 4.2 The patients have major deviations from protocol if they:

- have not received operative treatment in accordance with randomized allocation.
- have received operative treatment in accordance with randomized allocation and operated with a new operation at same level during the follow-up period.
- have not provided informed consent.
- have withdrew the informed consent and claimed their data withdrawn from analyses.

## **Statistical analyses**

All statistical analyses will be performed by a statistician blinded to the treatment given. Since this is a large randomized controlled trial, we will likely not need to adjust for potential confounding factors. However, if descriptive statistics reveal that there are imbalances in the study groups we will make comparisons with proper adjustments for such imbalances.

When comparing changes in outcomes from baseline to a fixed time point (e.g. 2, 5 or 10 years) we will use ANOVA combined with post-hoc testing for continuous outcomes. For categorical outcomes we will use standard chi-square analyses. If there is a need for confounder adjustment we will estimate the proper regression models dependent on the level of measurement of the dependent variable. Multilevel models might be used to analyse repeated measures data.

When trying to identify factors that could serve as predictors for outcome we will estimate multivariable regression models. The following factors are a priori considered to be the most relevant: treatment group, age, sex, BMI, smoking, preoperative dural sac cross-sectional area (in mm^2), percentage achieved decompression, preoperative ODI-score and preoperative NRS-score for leg pain and back pain. Bayesian information criterion (BIC) might be used as a statistical tool to select the best performing model.

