### **Justification for SAP revision:**

Update January 2016 From the start of inclusion (April 15, 2014) patients with ODI scores less than 25 were excluded. Due to experiences from participating surgeons that a considerable part of the patients was excluded due to ODI less than 25, even if their complaints from leg and back did justify an operation. To enhance the external validity of the study, the steering committee decided that from date 29th August 2015, the patients should not be excluded due to ODI- score lower than 25.

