## **Randomization**

Eligible patients are randomised into one of three arms, unilateral laminotomy with crossover, bilateral laminotomy and spinous process osteotomy with a 1:1:1 allocation. A randomized block design, stratified by hospital and the blocks made as small as possible, is used to ensure equal distribution of all three treatments (randomly selected block size 4 and 6).

Randomisation is performed in the 6 weeks before surgery. The randomisation procedure is concealed and administered by a study coordination centre at a university hospital and communicated to a local research coordinator who is not involved in the treatment of the patients. Randomisation is performed after the patient has signed the informed consent form. The result of the randomisation is documented in the patient record. Hence, neither the patients nor the surgeons can influence the type of intervention.

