## **Patient reported outcome measures (PROM)**

### **1) Primary outcome:**

The primary outcome is change in the Oswestry Disability Index (ODI) Norwegian version 2.0 [6] from baseline to 2-year follow-up. The ODI includes 10 questions about pain and activities of daily living. Each item has five response categories from no pain related disability (0) to the worst possible pain related disability (5). Responses are transformed into

an index ranging from no disability (0) to the worst possible disability (100). The ODI questionnaire is the most widely used and validated outcome measure in spinal surgery [7] [8].

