**Statistics:**

We have previously discussed that MCID is around 10-12 ODI-points for this group of patients. This value indicates the individual effect of treatment versus no-treatment. There is today no consensus in the literature of a clinically important difference between treatment groups. We have therefore decided that we want to reveal a difference of 7 ODI-points between the groups. A statistician has calculated a difference of 7 ODI-points between the treatment groups, and in a regular superiority design. Standard deviation is set to 18. Because we have three groups we want to compare the significans-level is lowered from 5% to 2% ( $p = 2$ ). The analyzes in the treatment group is done in the following way: -A compares with B, - A compares with C, -B compares with C.). With 80% power , significans level of 2%, and dropout of 30% n in each group is estimated to 187 (131 + 56). 30% dropout is a high

number, but we are planning to monitor the patients for 10 years, so we must anticipate a high dropout number. If we have problems to achieve 187 in each group, we will settle with 15% dropout. This gives 155 patients in each group.

We will also perform descriptive analyzes. The superiority analyzes is conducted in a One-way Anova system and Post Hoc.

Therefore we are planning to include 561 patients over a 2-3 year period. The analysis is conducted after the Intention To Treat Principle (ITT). Crossovers will be analyzed in the group they were originally randomized into. A sensitivity analysis will be conducted where patient crossing over from one treatment to another will receive the last score before crossover. Dropouts will be registered with the last value before dropout (last value carried forward).

Department of Clinical Research Support, at Oslo University Hospital will provide the block randomisation, and is performed within a computer program called Medinsight. The randomization process cannot be influenced by participating hospitals, and will be performed within 1 month before treatment.

Patient-data, and registration will also be handled by the computer programme called Medinsight.

The research protocol will be registered in [www.clinicaltrials.gov](http://www.clinicaltrials.gov).

The reporting of the trial will be bases on an adapted CONSORT (Consolidated Standards of Reporting Trials) checklist for reporting in randomised trials [18].

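### The primary ODI comparison omits baseline ODI and hospital as model terms and adjusts only if imbalance is seen; one pre-specified adjusted model would gain precision at no cost

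*Combined protocol and SAP*

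**What the plan says.** The SAP defines the endpoint under Primary outcome: "The primary outcome is change in the Oswestry Disability Index (ODI) Norwegian version 2.0", measured from baseline to the 2-year follow-up. Under Statistical analyses it says that for changes to a fixed time point "we will use ANOVA combined with post-hoc testing for continuous outcomes". The protocol's Statistics section agrees: "The superiority analyzes is conducted in a One-way Anova system and Post Hoc". A one-way ANOVA has arm as its only factor.

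On covariates, the SAP expects that "we will likely not need to adjust for potential confounding factors", and then adds that "if descriptive statistics reveal that there are imbalances in the study groups we will make comparisons with proper adjustments for such imbalances". The form of the adjusted analysis is left open: "If there is a need for confounder adjustment we will estimate the proper regression models dependent on the level of measurement of the dependent variable". The SAP does not list the variables to be inspected, define an imbalance, or say whether the adjusted or the unadjusted result would be primary.

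The SAP's Randomization section describes allocation as "stratified by hospital and the blocks made as small as possible". Hospital appears in no treatment comparison. As model terms, preoperative ODI appears only in the predictor analyses (SAP, Statistical analyses; protocol, Supplementary analysis I), and hospital only in the protocol's supplementary logistic regression of success. Baseline ODI is collected before surgery (SAP, Timeline). The analysing statistician is blinded to treatment.

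**The concern.** Two things are at stake.

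The first is precision. A change score subtracts baseline ODI with a fixed coefficient of 1. Unless the true slope of 2-year ODI on baseline ODI is 1, some variance that baseline could explain stays in the error term. The investigators already treat preoperative ODI as one of the most relevant predictors, so leaving it out of the main comparison gives up information they hold. Hospital is a smaller instance: allocation was balanced within hospital, but the analysis does not use that.

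The second is definition. Whether to adjust, for which variables and in what model would all be settled after the baseline tables are seen, so the trial has several candidate primary p-values. Under randomisation any baseline imbalance is due to chance. The reason to adjust is that a variable is prognostic, and that can be specified beforehand.

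**Working it through.** **Inputs from the documents.** Difference 7 ODI points, SD 18, alpha 0.02 per pairwise comparison, power 80%. The SAP has 155 per arm with 15% dropout. The protocol has 131 evaluable per arm, 187 with 30% dropout, and 15 planned hospitals. Sidedness is not stated, nor is whether 18 is the SD of change or of a score at one time.

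**Assumed inputs.** The correlation r between baseline and 2-year ODI, the ratio of their SDs, and the hospital intraclass correlation (ICC). The documents give none of these.

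**1. The plan's own figure.** With two sides and no covariates, n = 2 × 18² × (2.326 + 0.842)² / 7² = 132.7, so 133 per arm. Inflated: 133/0.85 = 157 and 133/0.70 = 190. The stated 131, 155 and 187 are all within three patients. A one-sided calculation gives 111 and does not reproduce them. The trial was therefore sized for a two-sided unadjusted comparison. Power at 131 per arm (noncentral t) is 79%.

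**2. Baseline ODI, 18 read as the SD of change, equal SDs.** With SD s at each time, the change-score variance is 2s²(1 − r) and the ANCOVA residual variance is s²(1 − r²). The ratio is (1 + r)/2, so the residual SD is 18 × √((1 + r)/2).

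| r | Variance ratio | Residual SD | Power, ANOVA | Power, ANCOVA |
|---|---|---|---|---|
| 0.3 | 0.65 | 14.5 | 79% | 94% |
| 0.4 | 0.70 | 15.1 | 79% | 92% |
| 0.5 | 0.75 | 15.6 | 79% | 90% |
| 0.7 | 0.85 | 16.6 | 79% | 86% |

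**3. The same reading, unequal SDs.** With baseline SD b and follow-up SD f, the ratio is f²(1 − r²) / (b² + f² − 2rbf). Assume b of 14–15, f of 18–20 and r of 0.3–0.5.
- Lowest ratio (b 15, f 18, r 0.3): 294.8/387 = 0.76.
- Highest ratio (b 14, f 20, r 0.5): 300/316 = 0.95.

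Applying these ratios to SD 18 gives residual SDs of 15.7 to 17.5 and power of about 90% down to 81%, against 79% unadjusted.

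**4. 18 read as the SD at one time.** The change SD is 18 × √(2(1 − r)) and the ANCOVA SD is 18 × √(1 − r²).

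| r | SD of change | Power, ANOVA on change | ANCOVA SD | Power, ANCOVA |
|---|---|---|---|---|
| 0.3 | 21.3 | 63% | 17.2 | 83% |
| 0.4 | 19.7 | 70% | 16.5 | 86% |
| 0.5 | 18.0 | 79% | 15.6 | 90% |
| 0.7 | 13.9 | 96% | 12.9 | 98% |

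**5. Hospital.** One pairwise comparison was simulated 20,000 times per setting: 131 per arm, 15 hospitals, arms balanced within hospital, total SD 18.

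| ICC | Type I error without / with hospital | Power without / with hospital |
|---|---|---|
| 0.05 | 0.018 / 0.021 | 80.0% / 81.5% |
| 0.10 | 0.015 / 0.021 | 80.2% / 83.3% |

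The nominal level is 0.02. Without the hospital term the test is slightly conservative.

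**The case against.** The best defence is that nothing here is an error. One-way ANOVA on change is unbiased under randomisation, and the sample size was derived without covariates. The trial therefore keeps about its planned power if 18 is the SD of change; it only forgoes a gain. The default analysis is stated consistently in both documents, and the blinded statistician limits steering towards a favoured arm. The gain also depends on r and on the SD ratio: in the least favourable corner of step 3 it is about 2 points. All of this stands and sets the severity. It does not settle which result is primary once the imbalance clause is used, because blinding to arm does not fix the covariates or the model.

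A reader might infer more than the documents support:

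- *That the planned test is invalid or its standard errors seriously wrong.* Omitting hospital errs on the conservative side, by a small amount.
- *That the trial is underpowered at 63–70%.* That needs 18 to be a single-time SD and r to be 0.3–0.4. The documents state neither, and at r = 0.7 the same reading gives 96%.
- *That a spurious imbalance would be flagged with a calculable probability.* The SAP speaks of descriptive statistics, not significance tests, and lists no variables, so no such probability can be derived.
- *That the eligibility change has measurably increased the loss.* The SAP records that from August 2015 "the patients should not be excluded due to ODI- score lower than 25". This would be expected to widen the baseline range, but no baseline SD is given under either rule, so the effect cannot be sized.
- *That baseline ODI is ignored altogether.* It is subtracted in the change score; what is missing is its use as a covariate.

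**Conclusion.** The point holds as a matter that should be fixed, not as a flaw that invalidates the analysis. The primary model leaves out a covariate the investigators themselves regard as relevant and the factor used to stratify allocation. The adjustment clause leaves the primary result undefined if it is invoked.

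Most of the recoverable precision comes from baseline ODI. If 18 is the SD of change, power rises from 79% to somewhere between about 81% and 94% over the assumptions shown. If 18 is a single-time SD, the gain runs from about 20 points at r = 0.3 (83 − 63) to 2 points at r = 0.7 (98 − 96). Hospital adds roughly 1.5–3 points at an ICC of 0.05–0.10. In every scenario computed here ANCOVA has at least as much power as the planned test. The amount rests on r, the SD ratio and the ICC, all of which are assumptions.

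**What to change.** In the SAP's Statistical analyses section:

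- Pre-specify one primary model for 2-year ODI with arm, baseline ODI and hospital, and take the three pairwise arm contrasts at the planned 2% level. With baseline ODI in the model, analysing 2-year ODI or its change gives the same arm contrasts, so the primary outcome need not be redefined.
- Say how sparse hospitals are handled. With 155 per arm over 15 planned hospitals the average is about 10 per arm per hospital (155/15), so some may be small. A random hospital effect or pooling of small sites would serve.
- Use the same form for other continuous outcomes that have a baseline value.
- Delete the adjustment triggered by observed imbalance.
- Keep the unadjusted one-way ANOVA as a sensitivity analysis.
- The planned comparison of success proportions may stay. A logistic model with baseline ODI and hospital is an optional supplement.

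The cost is SAP wording only. Baseline ODI and hospital are already recorded, and the sample size need not change.

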## **Sample size**

The trial is planned with a superiority design. The study is designed to detect a difference of 7 ODI-points between the groups. With a standard deviation of 18, a significance level of 0.02, 80% power and a drop-out rate of 15%, we need to include 155 patients in each group. Thus, we plan to include 465 patients over a 4-5 year period. The analysis will be performed according to the intention to treat principles. If the number of drop-out or missing data exceeds 15%, imputation will be performed

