**Exclusion criteria:**

- have a degenerative lumbar spondylolisthesis, with a slip  $\geq 3$  mm verified on standing plain x-rays in lateral view.
- -are not willing to give written consent.
- -have former surgery in the level of stenosis.
- -fracture, or former fusion of the thoracolumbal region.
- -cauda equina syndrom (bowel or bladder dysfunction) or fixed complete motor deficit.
- -are ASA- classified 4 or 5.
- -are older than 80 years
- -have a lumbosacral scoliosis more than 20 degrees verified on AP-view
- -have **distinct** symptoms in one or both of their legs due to other diseases, e.g. polyneuropathy, vascular claudication or osteoarthritis.
- -LSS in 4 or more levels.

- -not able to comply fully with the protocol, including treatment, follow-up or study procedures (psychosocially, mentally and physical).
- the patient is participating in another clinical trial that may interfere with this trial

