### **During the hospital stay:**

- The surgeon will register radiological findings, ASA-classification, operation method, operation time, level and blood loss, and per-operative complications.
- Complications will be registered during follow-up by an independent nurse or physician.

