## **Operative differences**

As mentioned earlier, there are differences between the three surgical methods. We are planning to observe whether there are significant differences between the methods as regards operation time, amount of peri-operative bleeding, peri-operative complications and length of hospital stay. And, we will also examine whether one of the three surgical procedures have an increased rate of reoperations in the observation period. Thereby we are able to monitor costs of each of the three methods.

We also want to find out whether any of the surgical methods preserves stability better than the others. Preoperative standing x-rays, with lateral view of flexion-extension of the lumbosacral spine are therefore important as a baseline. In the follow up period we will repeat these x-ray investigations and thus find out if any of the methods is more prone to postoperative instability.

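### Operation time, bleeding and hospital stay are to be compared between techniques, but no analysis is specified for them and none adjusts for the number of stenotic levels

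*Combined protocol and SAP*

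**What the plan says.** The protocol, under Operative differences, plans to look for "significant differences between the methods as regards operation time, amount of peri-operative bleeding, peri-operative complications and length of hospital stay". It ties this comparison, together with reoperations, to monitoring the cost of each method. No test is named there. The SAP, under Secondary outcomes, says that the coordinator records hospital stay, duration of surgery and blood loss, and gives no analysis for them.

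The SAP's Statistical analyses section says "we will use ANOVA combined with post-hoc testing for continuous outcomes", in a sentence that concerns changes from baseline to a fixed time point. The protocol's Statistics section names one-way ANOVA with post-hoc tests for its superiority analyses. The SAP expects that adjustment will probably not be needed and provides for it only if descriptive statistics show imbalance.

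On the number of levels:
- The exclusion criteria rule out "LSS in 4 or more levels", so patients with one, two or three levels can enter.
- Randomisation is stratified by hospital only.
- During the hospital stay the surgeon registers "operation method, operation time, level and blood loss, and per-operative complications".
- The SAP's list of predictors omits level. The protocol's Supplementary analysis I includes level of stenosis, but only in the model for success at 24 months.

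Neither document mentions a transformation or another method for skewed data.

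**The concern.** An operation on three levels can be expected to take longer, and usually to bleed more, than an operation on one. If patients with one to three levels are pooled and compared without regard to that number, the variation between levels goes into the error term. Randomisation balances it on average, so the estimated difference between techniques stays unbiased, but its standard error is larger than it needs to be. A real but moderate difference in operation time could then be missed, in a comparison that the protocol states as a question and uses for its cost aim.

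Adjustment triggered by observed imbalance does not repair this. The loss of precision is present even when the arms are perfectly balanced, and a rule that waits for the data leaves the model open.

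**Working it through.** **The plan's own figure.** The SAP's Sample size section says "The study is designed to detect a difference of 7 ODI-points between the groups" and continues "With a standard deviation of 18, a significance level of 0.02, 80% power and a drop-out rate of 15" per cent. For a two-sided comparison of two means, n = 2 × (2.326 + 0.842)² × 18² / 7² = 132.7, so 133 evaluable per group. The protocol uses 131, and 131 / 0.85 = 154.1, which gives the stated 155. The figure reproduces closely (133 / 0.85 gives 157). It concerns ODI and says nothing about operative outcomes.

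**Inputs for operation time.**
- From the documents: 155 per arm (SAP, Sample size) and the 2% level for pairwise comparisons (protocol, Statistics). Dropout hardly matters, since the outcome is recorded during the hospital stay.
- Assumed, because the documents give nothing: 60%, 30% and 10% of patients with one, two and three levels; residual SD 30 min within a level count; a true difference of 10 min; 10, 20 or 35 min added per level.

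**Formulas.**
- Variance of the level count: mean = 0.6 × 1 + 0.3 × 2 + 0.1 × 3 = 1.5; variance = 0.6 × 0.25 + 0.3 × 0.25 + 0.1 × 2.25 = 0.45.
- Unadjusted SD = √(30² + b² × 0.45), where b is the minutes added per level. Adjusted SD = 30.
- SE = SD × √(2/155) = SD × 0.1136.
- Power is taken from the two-sided t-test at 2%; it is close to Φ(10/SE − 2.326).

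| Minutes per level | Variance explained by levels | SD unadjusted | SE unadjusted | Power unadjusted | SE adjusted | Power adjusted |
|---|---|---|---|---|---|---|
| 10 | 45/945 = 5% | 30.7 | 3.49 | 70% | 3.41 | 72% |
| 20 | 180/1080 = 17% | 32.9 | 3.73 | 63% | 3.41 | 72% |
| 35 | 551/1451 = 38% | 38.1 | 4.33 | 49% | 3.41 | 72% |

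Simulation of the same settings gave 48–70% unadjusted and 71–73% adjusted.

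**Log scale for operation time.** In the same simulated settings, with an assumed one-level mean of 70 to 130 min, adjusting on the log scale gave about 61–71%. That is below adjustment on the minute scale, and for the shorter means with a modest level effect it is no better than plain ANOVA.

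**Blood loss and stay** (simulated as log-normal, same level mix, all inputs assumed).
- Blood loss, residual log-SD 0.8, ratio 1.3: raw 51%, raw plus levels 54%, log 69%, log plus levels 74%. Here most of the gain comes from the scale.
- Blood loss, log-SD 0.6–0.8, 0.4–0.5 log units per level, ratio 1.25: about 31–62% raw and 54–82% on the log scale with levels.
- Hospital stay, log-SD 0.5, ratio 1.2: raw 71%, raw plus levels 73%, log plus levels 79%.
- For large differences every version has power near 100%. With no true difference, the raw test rejected in 1.4–2.6% of runs, in line with the nominal 2%.

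**The case against.** The strongest objection is that the quoted ANOVA sentence does not govern these outcomes. They have no baseline value, and the protocol's ANOVA statement stands in a section about the ODI sample size. A reader might infer that the plan commits the operative comparison to plain ANOVA and so throws away much of its power. The documents do not support that: strictly, no analysis is specified. What stands is that neither the literal reading nor the generous one, with ANOVA as the default, uses the number of levels.

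Second, the size of any loss is assumed. The documents give no SD, skew, level mix or effect per level, and the gain may be about 2 percentage points. This is correct.

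Third, the outcomes are secondary, the comparison is announced only in the protocol while the SAP merely records the data, and adjustment is allowed if imbalance appears. All true. This limits the weight of the point, but conditional adjustment still leaves the model undefined.

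Fourth, a reader might infer from the likely skew that everything should be analysed on the log scale. That does not follow. It lowers power for operation time in the scenario above, it compares geometric means whereas costs follow arithmetic means, and it is undefined for zero blood loss.

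Fifth, a preoperative level count is implied by the eligibility check but does not appear in the list of data collected before surgery, and the level registered at operation may be an anatomical site. This stands and is part of the cost of the change.

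**Conclusion.** The point holds as a matter of precision. The operative comparison is a stated question, no analysis is specified for it, and a probable source of variation that can be known before randomisation is left out. For a 10-minute difference in operation time, adjustment for levels raises power from about 70% to 72% at 10 minutes per level and from about 49% to 72% at 35 minutes per level, given residual SD 30 min, a 60/30/10% level mix, 155 per arm and a 2% level. For blood loss and stay, adjustment for levels alone adds about 2 to 4 percentage points in the simulated cases.

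The documents do not support a claim of bias or of inflated type I error, nor a claim that a large loss of power is established. The primary ODI analysis is untouched. The level adjustment is the firm part of the recommendation; the log scale is a secondary choice for blood loss.

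**What to change.** Add to the SAP's Statistical analyses section that operation time, blood loss and length of stay are compared between techniques by linear regression, with technique and the preoperative number of stenotic levels (1, 2, 3) as covariates fixed in advance, whether or not imbalance is observed. Report adjusted mean differences with confidence intervals for the three pairwise comparisons.

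Take the level count from the eligibility assessment or the preoperative MRI. Do not use the number of levels finally operated, which is settled after randomisation and could depend on the technique.

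For blood loss, if it is right-skewed, a log-scale analysis with the same covariate and a stated rule for zero values may be added. Keep the arithmetic means for the cost aim.

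The cost is slightly more analysis work, and the preoperative level count must be retained in the database or read from the existing MRI scans. No extra patients or visits are needed.
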